### Ethical Considerations

#### Overview

The trial has been approved by the NIMHANS Human Ethics Committee for Research in AYUSH and Integrative Medicine (NIMHANS/HECAIM/5th/MEETING/2021‐2022, dated January 7, 2022). All procedures in the trial will comply with the ethical guidelines outlined by the Indian Council of Medical Research and the Declaration of Helsinki [14,17]. Participants will be recruited only after obtaining written informed consent, ensuring that they fully understand the study’s objectives, interventions, potential risks, and benefits. The study is covered by trial insurance from the Oriental Insurance Company. Confidentiality of the study participants will be ensured by anonymization of the data.

#### Consent

Informed consent will be obtained by the SRF possessing an MD (Ayurveda) qualification, who has been trained in GCP [14] and institutional ethical guidelines for human research. The SRF has prior experience in conducting clinical studies and in obtaining informed consent in accordance with ethical standards.

The consent process will be conducted in the participant’s preferred language, ensuring adequate explanation of study objectives, procedures, potential risks, and benefits. Ample time will be provided for participants to ask questions and decide about participation voluntarily. The entire process will be documented, and a copy of the signed consent form will be provided to each participant.

Any AEs occurring during the course of the trial will be promptly reported to the Data and Safety Monitoring Board (DSMB) as per the approved protocol. Participants experiencing an AE will receive appropriate and immediate clinical care. Each event will be independently reviewed by a committee comprising experts from both the Ayurveda system of medicine and modern medical sciences.

If, upon thorough evaluation, the AE is determined to be related to the investigational intervention, compensation will be provided to the participant in accordance with regulatory requirements through the study’s approved insurance coverage.

### Brief Description of Some Relevant Assessments

#### Clinical Assessments

##### Movement Disorder Society–Unified Parkinson’s Disease Rating Scale

This scale assesses motor and nonmotor PD symptoms. It includes four parts: nonmotor experiences of daily living (part I), motor experiences of daily living (part II), motor examination (part III), and motor complications (part IV). Parts IA, IB, and II are conducted in the “ON” state, whereas Part III is assessed in both “ON” and “OFF” states. Part IV integrates patient-reported information with clinical observations [18].

##### Unified Dyskinesia Rating Scale

This tool evaluates involuntary movements (dyskinesia) associated with PD treatment. It includes historical (on-dyskinesia and off-dystonia) and objective (impairment and disability) sections, focusing on choreic and dystonic movements [19].

##### Scales for Outcomes in Parkinson’s Disease–Sleep

This assesses nighttime and daytime sleep problems over the past month. It includes subscales for nighttime sleep and daytime sleep, with a global assessment of nocturnal sleep quality [20].

##### Montreal Cognitive Assessment

This tool evaluates cognitive function, assessing memory, language, executive functions, visuospatial skills, attention, abstraction, and orientation. It provides a Derived Memory Index score to predict Alzheimer dementia conversion [21,22].

##### 10-m Walk Test and 6-Minute Walk Test

These assess gait. The 10-m walk test measures gait speed, whereas the 6-minute walk test evaluates aerobic capacity and endurance. Both are performed in the “OFF” state [23,24].

##### Balance Error Scoring System

This measures postural stability using the Biodex balance system. It involves 3 stances (double-leg, single-leg, tandem) performed on firm and foam surfaces with eyes closed. Errors are scored, with lower scores indicating better balance [25].

##### Transcranial Magnetic Stimulation

This noninvasive technique assesses motor cortical function. TMS is conducted through “Magventure R30 with magoption” equipment using the MCB-70 coil. It measures parameters such as resting MT (RMT), central motor conduction time, SP, SICI, LICI, and ICF. It is performed in the “OFF” state [26].

##### Heart Rate Variability

This assesses autonomic function using the “Chronovisor” HRV machine. Time-domain (SDNN, pNN50, RMSSD) and frequency-domain (low frequency, very low frequency, ultra low, high frequency, and low frequency–to–high frequency ratio) measures are acquired in the “OFF” state.

##### Pulmonary Function Test

This evaluates respiratory capacity using spirometry. Lung volume measures (forced vital capacity, forced expiratory volume in 1 s, and forced expiratory volume in 1 s–to–forced vital capacity ratio) and respiratory muscle strength (MIP and MEP) are assessed in the “OFF” state.

### Neuroimmune Parameters

#### Objectives

The objectives are to assess (1) the proportions and activation status of human peripheral blood Th1/Th2/Th17 cells and (b) the estimation of cytokine by Cytometric Bead Array.

#### Peripheral Blood Mononuclear Cell Isolation and Cryopreservation

Peripheral blood mononuclear cells (PBMCs) and plasma samples will be separated from peripheral whole blood samples (10 mL) by density gradient centrifugation and cryopreserved.

### Procedure

#### Staining With Fluorescent Antibodies for Immunophenotyping of Th1/Th2/Th17 Cells

Cryo-preserved PBMCs will be processed for multiparametric assessment of the frequencies of major adaptive immune T cells, namely Th1, Th2, Th17, and Treg cells. Briefly, 1 million PBMCs for each panel of immune surface markers will be stained with LIVE/DEAD Fixable green (Life Technologies) to exclude dead cells and with respective antibodies for 20 and 30 minutes, respectively, at 4°C. Cells will be washed and resuspended in 0.5% paraformaldehyde for fixation. Finally, the cells will be washed and resuspended in phosphate-buffered saline (containing 1% fetal bovine serum). An unstained control will be included with all samples. Stained samples will be acquired using a FACSLyric (BD Biosciences) flow cytometer. Analysis is done by using FlowJo software. Quality control of flow cytometry analysis will be ensured by monitoring the performance of the instrument using Cytometer Setup and Tracking beads. Compensation for fluorescence spectral overlaps will be calculated and applied for the analysis of data for each of the different antibody cocktails. Data will be acquired through the BD FACSuite interface and analyzed on FlowJo software (Table 1).

**Table 1. T1:** Design of fluorescent antibody panel based on the lasers and detection filters available in the FACSLyric flow cytometer for the identification of Th1, Th2, and Th17 cells.

Lasers and antibody marker		Fluorochrome
Violet laser (405 nm)		
Anti-CD4		BV 421
Anti-CD25		BV 605
Anti-CD127		BV 750
Blue laser (488 nm)		
Anti-CCR6[CD 196]		Alexa Fluor 488
Anti-CD8		PE
Anti-CCR4[CD 194]		PE CY 7
Anti-FoxP3		BB 700
Red laser (640 nm)		
Anti-CD3		AF 647
Anti-CXCR3[CD 183]		BD Horizon R 718

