### Outcome Measures

The primary outcome is the change in the total score of the Movement Disorder Society-UPDRS (MDS-UPDRS) after 6 months of treatment, compared with the baseline. MDS-UPDRS Part III will be assessed in both the ON and OFF medication states. The OFF state assessment will be conducted after a 12-hour withdrawal from the patient’s last dopaminergic medication, whereas the ON state assessment will be performed 1 hour after the administration of the first morning dose of dopaminergic medication. The OFF-state evaluation (after 12 h withdrawal) reflects the underlying disease severity, whereas the ON-state evaluation (1-h postmorning dose) reflects treatment responsiveness. The total MDS-UPDRS change is thus intended to integrate both clinical states, which is relevant for this exploratory phase of the Ayurvedic add-on intervention assessment.

The secondary outcome measures include a range of neurophysiological, biochemical, cognitive, and functional parameters. Cortical excitability will be assessed using TMS, evaluating both single-pulse (MT, resting cortical, and SP) and paired-pulse (SICI, LICI, and ICF) measures. Autonomic function will be analyzed through HRV, whereas pulmonary function tests will assess respiratory capacity.

Exploratory mechanistic outcomes include alterations in immunological markers, including changes in Th1/Th2/Th17/T regulatory cell populations, plasma levels of pro-inflammatory cytokines, and telomere length, which will be measured to evaluate the immunomodulatory and anti-inflammatory effects of the intervention.

Functional and motor outcomes will be examined through reductions in dyskinesia severity using the Unified Dyskinesia Rating Scale and improvements in gait parameters, measured using the 6-minute walk test and gait speed (10-m walk test). Cognitive function will be assessed using the Montreal Cognitive Assessment, and postural stability will be evaluated through the Balance Error Scoring System. Changes in Scales for Outcomes in Parkinson’s disease-Sleep will be monitored to assess improvements in sleep disturbances associated with PD.

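### The green viability dye and CCR6 on Alexa Fluor 488 appear to fall in one detector, so Th17 gating is confounded with post-thaw cell viability

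*Protocol article*

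**What the plan says.** The staining section under Procedure takes "1 million PBMCs for each panel of immune surface markers" and says that they "will be stained with LIVE/DEAD Fixable green (Life Technologies) to exclude dead cells and with respective antibodies". The incubations run "for 20 and 30 minutes, respectively, at 4°C". The next step is "Cells will be washed and resuspended in 0.5% paraformaldehyde for fixation", followed by a wash into buffered saline and acquisition. Compensation is planned for every antibody cocktail, and the one control named is an unstained sample.

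Table 1 is the only panel shown. It lists:
- violet laser: CD4, CD25 and CD127;
- blue 488 nm laser: CCR6, CD8, CCR4 and FoxP3;
- red laser: CD3 and CXCR3.

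CCR6 carries "Alexa Fluor 488" and FoxP3 carries BB 700. The viability dye is not in the table, and no detector is given for it.

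Outcome Measures places "changes in Th1/Th2/Th17/T regulatory cell populations" among the exploratory mechanistic outcomes, while Objectives lists immune parameters under the secondary objectives. Hypothesis expects a shift in these populations that correlates with clinical, cognitive and neurophysiological results. Table 2 schedules the measurement at baseline and day 180.

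**The concern.** A viability dye works only if its signal can be told apart from every antibody in the tube. Here a green dead-cell dye and a green antibody label are combined. A green-positive event may then be a dead cell or a live CCR6+ cell. If all green-positive events are discarded as dead, live CCR6+ cells go with them. If they are kept, dead cells are counted as CCR6+.

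The cells are cryopreserved, so some loss of viability on thawing is to be expected, and it may vary between vials. The apparent Th17 fraction would then partly follow sample handling. That weakens the within-participant change from baseline to day 180 and the planned correlations with clinical outcomes.

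Separately, FoxP3 lies inside the nucleus, but the steps as written describe a surface stain.

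**Working it through.** The plan gives no figure to reproduce, so the check sets the staining text beside Table 1.

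1. **Is the dye in the tube with CCR6?** Yes, as written. The staining sentence applies to each panel, and Table 1 is the only panel shown.
2. **Do the labels overlap?** The documents name no detector for the dye. The inference comes from the reagents: a green fixable dye and Alexa Fluor 488 are both excited at 488 nm and both emit green.
3. **Does the planned compensation solve it?** No. Compensation subtracts spillover between detectors. It cannot divide the signal in one detector between two labels with near-identical spectra.
4. **Can another marker replace CCR6?** The nine antibodies are CD3, CD4, CD8, CD25, CD127, CXCR3, CCR4, CCR6 and FoxP3. Th2 and Th17 cells both typically express CCR4 and lack CXCR3, so within this panel CCR6 is what separates them. Th1 or Th2 gates that require CCR6-negative cells inherit the problem. The article does not state the gates.
5. **FoxP3.** The antibodies go on before the only fixation step, and neither permeabilisation nor a second stain follows. CD25 and CD127, both surface markers, are in the same panel.

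**Illustration only; no input comes from the documents.** Let the true CCR6+ fraction of live cells be 20%, let d be the fraction of dead cells, and let f be the share of dead cells that falls inside the CCR6 gate, with the other dead cells excluded. Then

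apparent CCR6+ = (0.20(1 − d) + f·d) / ((1 − d) + f·d).

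- f = 0.5, d = 0.10: (0.18 + 0.05)/(0.90 + 0.05) = 0.23/0.95 = 24%.
- f = 0.5, d = 0.30: (0.14 + 0.15)/(0.70 + 0.15) = 0.29/0.85 = 34%.
- f = 0: 0.18/0.90 = 0.14/0.70 = 20%, so no distortion.
- f = 1: 0.28/1.00 = 28% at d = 0.10 and 0.44/1.00 = 44% at d = 0.30.

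At f = 0.5 the excess due to dead cells is 4 to 14 percentage points. The result depends heavily on f, about which the article says nothing. The sketch also ignores the other Table 1 markers, which would restrict the events counted.

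**The case against.** The strongest reply is that this is a condensed article. The staining paragraph announces itself as a summary and mentions more than one cocktail, so a laboratory procedure may hold what is missing here. For FoxP3 that carries weight: an unmentioned permeabilisation step is not one known to be absent, and a separate intracellular stain is not ruled out. It carries less weight for the dye, because there the issue is two named reagents that conflict, not an omitted detail.

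A reader might go further and infer that Th17 and regulatory T cells cannot be measured at all. The documents do not support that. Very bright dead cells could be partly gated out, so the Th17 fraction is confounded, not lost. Regulatory T cells can still be defined by CD25 and CD127, and the article fixes no gate that relies on FoxP3 alone.

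A reader might also infer a false treatment effect. Nothing in the article suggests that post-thaw viability differs between the randomised arms. Without such a difference, the likely harm is noise and a blurred measure, not bias in favour of one arm.

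Nor do the documents justify a blanket rule against reporting samples already run. They do not say whether any have been acquired, or whether the reagents used match the text.

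**Conclusion.** The point stands in limited form. As written, the green viability dye conflicts with CCR6 on Alexa Fluor 488, and this confounds dead-cell exclusion and CCR6-based subsets with viability after thawing. The conclusion rests on spectral overlap inferred from the reagent names and on Table 1 being the panel actually used.

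The size of the error cannot be derived from the documents, and the percentages above only illustrate the mechanism. The FoxP3 point is secondary: the written order does not suit an intranuclear target and needs reconciling, but the article may simply have left a step out.

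The effect is confined to the exploratory T-cell subset outcomes and their correlations. The primary outcome, sample size, power and safety monitoring are untouched, and plasma cytokines, C-reactive protein and telomere length do not depend on this panel.

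**What to change.** Before further acquisition:

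- Move the viability dye, or CCR6, to a detector that Table 1 does not use, and add the dye and its channel to Table 1. If the laboratory already does this, correct the text.
- Process each participant's baseline and day-180 samples with the same revised panel, so that a change of reagent is not mistaken for a change over time.
- For samples already acquired, report CCR6-based subsets only if dead cells and CCR6+ cells can be shown to be separable. Otherwise flag this as a limitation.
- Reconcile the FoxP3 staining with the laboratory procedure: state the permeabilisation step, or define regulatory T cells as CD25high/CD127low with the markers already in the panel.

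The cost is one reagent change and a revised staining procedure. Cryopreserved samples not yet stained lose nothing. These subsets may be lost for samples already run. The article gives a single 10 mL draw and no count of stored vials, so a repeat run cannot be assumed.

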#### Estimation of Cytokine by Cytometric Bead Array

Cryopreserved plasma specimens will be processed according to the manufacturer’s instructions for the detection and quantification of the proposed cytokines using the Cytometric Bead Array kit (BD Biosciences). Data will be acquired on FACS Verse flow cytometer (BD Biosciences) and analyzed on FCAP Array software (BD Biosciences Table 2).

**Table 2. T2:** Participant enrollment and schedule of assessment.

Assessments	Baseline	60th day	120th day	180th day
MDS-UPDRS^a^	✓	✓	✓	✓
UDyRS^b^	✓	✓	✓	✓
SCOPA-S^c^	✓	✓	✓	✓
MoCA^d^	✓	✓	✓	✓
6-minute walk test Gait speed (10-m walk test)	✓	✓	✓	✓
BESS^e^	✓	✓	✓	✓
Laboratory parameters				
Hematology				
Complete hemogram	✓	—^f^	—	✓
ESR^g^	✓	—	—	✓
Biochemistry				
Liver function test	✓	✓	—	✓
Renal function test	✓	✓	—	✓
Lipid profile	✓	—	—	✓
HbA_1c_^h^	✓	—	—	✓
FBS^i^	✓	—	—	✓
Sr. Uric acid	✓	—	—	✓
Inflammatory markers				
Plasma cytokine assay	✓	—	—	✓
Immunophenotyping for Th1/Th2/Th17/T-regulatory cell population	✓	—	—	✓
TMS^j^				
Single pulse measures	✓	—	—	✓
Paired pulse measures	✓	—	—	✓
Neurophysiological parameters	✓	—	—	✓
HRV^k^	✓	—	—	✓
PFT^l^	✓	—	—	✓
Concomitant medication	✓	✓	✓	✓
Rescue medication	—	✓	✓	✓

a MDS-UPDRS: Movement Disorder Society–Unified Parkinson’s Disease Rating Scale.

b UDyRS: Unified Dyskinesia Rating Scale.

c SCOPA-S: Scales for Outcomes in Parkinson’s Disease–Sleep.

d MoCA: Montreal Cognitive Assessment.

e BESS: Balance Error Scoring System.

f Not available.

g ESR: erythrocyte sedimentation rate.

h HbA_1c_: glycated hemoglobin.

i FBS: fetal bovine serum.

j TMS: transcranial magnetic stimulation.

k HRV: heart rate variability.

l PFT: pulmonary function test.

### Plans for Data Storage, Handling, and Availability

Research investigators and study personnel will receive comprehensive, documented training on the protocol. Access to CRFs and electronic CRFs will be limited to trained individuals to ensure standardized data entry. MDS-UPDRS scores will be recorded on paper and cross-verified with electronic entries to minimize errors. Participant data will be coded, securely stored with password protection, and assigned unique identification codes for pseudonymization. The data analyst will be blinded to group allocation. PIs will ensure secure data sharing mechanisms for privacy and confidentiality.

Upon completion of the study, the deidentified research data will be submitted to and maintained jointly by CCRAS and the NIMHANS. The dataset will be stored in the research data repository managed by CCRAS. Access to the data can be requested by contacting the funding agency through the official CCRAS website [27] and submitting a formal request describing the intended use. Data will be shared upon reasonable request, subject to institutional approvals and applicable data sharing regulations. No public code repository is applicable for this protocol.

### Statistical Analysis

All analyses will be performed using SPSS software. The primary outcome, change in MDS-UPDRS Part III score from baseline to 24 weeks, will be analyzed using a mixed model for repeated measures with treatment, time, and treatment×time interaction as fixed effects and baseline values as covariates. LEDD will be included as a time-varying covariate to account for dopaminergic medication effects. Results will be reported as least-square mean differences with 95% CIs. The main analysis will follow a modified intention-to-treat approach including all randomized participants who receive at least one dose of the assigned intervention, whereas a per-protocol analysis will be performed as a sensitivity check on participants who complete ≥80% of scheduled therapies and medication adherence.

Missing data will be handled under the assumption of data missing at random using the mixed model for repeated measures model, which uses all available data without imputation. Additional sensitivity analyses, including multiple imputation and complete case analyses, will be performed to evaluate the robustness of results. The secondary outcomes will be analyzed using appropriate mixed or generalized linear models and interpreted as exploratory. Descriptive statistics will summarize categorical variables as frequencies and percentages, and continuous variables as mean (SD), median (IQR), and range.

Predefined subgroup analyses will explore whether treatment effects differ by baseline Hoehn and Yahr stage (≤3.0 vs >3.0), disease duration (<5 vs ≥5 y), age (<65 vs ≥65 y), baseline LEDD (≤ median vs >median), and presence of dyskinesia. Interaction terms will be tested using mixed effects models, and the results will be interpreted as exploratory. Sensitivity analyses will include assessing participants with stable dopaminergic doses (<10% LEDD change) and testing the interaction between treatment allocation and LEDD change to explore medication-dependent effects. Safety analyses will be descriptive, summarizing AEs and serious AEs by treatment group.

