**Methods:**

A total of 80 patients with PD, diagnosed according to UK Parkinson’s Disease Society Brain Bank criteria, will be randomized into two groups: TAU and add-on Ayurveda. The intervention group will receive Ayurvedic therapy alongside conventional treatment for 180 days, whereas the control group will continue TAU. Assessments will occur at baseline and at 60-, 120-, and 180-day follow-ups, evaluating motor and nonmotor symptoms. Transcranial magnetic stimulation, heart rate variability, and pulmonary function tests will assess cortical excitability, autonomic function, and pulmonary function, respectively. Immunological parameters, including cytokine levels and telomere length, will be analyzed at baseline and at 180 days to explore disease-modifying effects. Liver and renal function tests will monitor safety.

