### Sample Size

This study has been designed as an exploratory trial primarily aimed at assessing feasibility and generating preliminary clinical evidence on the effects of a multicomponent Ayurvedic add-on therapy in PD. The sample size estimation was based on parameters from a prior exploratory study [16], which reported a mean change in the Unified Parkinson’s Disease Rating Scale (UPDRS) score of 1.0 with an SD of 2.0 and a correlation coefficient of 0.60. Using these assumptions, a 2-tailed alpha of 0.05, and 80% power, the required sample size was calculated to be 28 participants per group. Allowing for a 20% attrition rate, a total of 40 participants per group (80 overall) will be recruited.

This sample size is expected to provide preliminary insights into the effects of add-on Ayurveda therapy in PD and to serve as a basis for future large-scale confirmatory trials.

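### The primary mixed model lists no baseline-by-time term, so one baseline slope serves all three visits; adding the term is a cheap, minor improvement

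*Protocol article*

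**What the plan says.** The Statistical Analysis section names the endpoint as "change in MDS-UPDRS Part III score from baseline to 24 weeks" and the analysis as a "mixed model for repeated measures with treatment, time, and treatment×time interaction as fixed effects and baseline values as covariates". It adds that "LEDD will be included as a time-varying covariate". The words that matter here are "interaction as fixed effects and baseline values as covariates": treatment×time is the only interaction listed for this model.

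On visits, the abstract says: "Assessments will occur at baseline and at 60-, 120-, and 180-day follow-ups". The model therefore has three post-baseline time points, and the primary contrast belongs to the last.

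The Sample Size section gives the only correlation in the article, from a prior exploratory study: a mean change in UPDRS "score of 1.0 with an SD of 2.0 and a correlation coefficient of 0.60". It ties that value to no visit and gives no SD by visit.

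Missing data are assumed missing at random and are handled through the same mixed model. The Harms section says that participants who discontinue or deviate from the intervention get no further outcome assessments. The Results section reports 58 enrolled, 33 completed, 14 discontinued and 11 continuing.

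**The concern.** In a repeated-measures model with an unstructured covariance, a single baseline slope is a weighted compromise across visits. If baseline predicts the score less strongly as time passes, that compromise lies above the slope that fits day 180. Two things follow.

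- **Precision.** The adjustment at day 180 is not the best one. Residual variance there is somewhat larger than it need be, at the visit where the treatment effect is read.
- **Dropout.** The missing-at-random analysis relies on this model for what it implies about unobserved day-180 scores. If the slope is wrong at day 180, and participants who leave differ in baseline severity between arms, the error does not cancel between arms and the treatment difference shifts.

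**Working it through.** **Inputs from the article.** SD 2.0, difference 1.0, correlation 0.60, "a 2-tailed alpha of 0.05, and 80% power", 40 per arm, 1:1 allocation, visits at days 60, 120 and 180.

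**Assumed, because the article does not give them.** Baseline correlations at days 60 and 120; 0.60 placed at day 180; equal SDs at all visits; correlations between follow-up visits that depend only on their spacing, with the same decay as from baseline. LEDD is left out of the check.

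**1. The plan's own figure.** The 28 per group is reproduced by a one-group paired t-test: SD of change = 2.0 × √(2 × (1 − 0.60)) = 1.789, which gives n = 28. A two-arm comparison adjusted for baseline has SD 2.0 × √(1 − 0.60²) = 1.6 and needs 41 per arm. That mismatch is a separate matter. Here 1.6 serves only as the SD for the power figures: at 40 per arm the standard error is 1.6 × √(2/40) = 0.358 and power for a difference of 1.0 is 79.8%.

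**2. Precision loss in large samples.** The slope at a visit is correlation × (visit SD / baseline SD), which equals the correlation when SDs are equal. Let b180 be the day-180 slope and bc the common slope from generalised least squares. Then

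variance ratio at day 180 = 1 + (b180 − bc)² × Var(baseline) / residual variance at day 180.

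With equal SDs the last factor is 1/(1 − 0.60²) = 1/0.64.

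| Assumed correlations, days 60/120/180 | bc | Variance ratio | SE ratio | Power at 40 per arm |
|---|---|---|---|---|
| 0.60/0.60/0.60 | 0.600 | 1.000 | 1.000 | 79.8% |
| 0.70/0.65/0.60 | 0.659 | 1.0055 | 1.003 | 79.6% |
| 0.80/0.70/0.60 | 0.750 | 1.0352 | 1.017 | 78.5% |
| 0.84/0.71/0.60 (first-order autoregressive) | 0.804 | 1.065 | 1.032 | 77.3% |
| 0.85/0.72/0.60 | 0.816 | 1.0728 | 1.036 | 77.0% |

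Example for the third row: (0.60 − 0.750)² / 0.64 = 0.0225 / 0.64 = 0.0352. The last row is equivalent to losing 80 × (1 − 1/1.0728) ≈ 5 participants; the second row, 80 × (1 − 1/1.0055) ≈ 0.4.

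**3. Check at the trial's size.** Restricted-likelihood mixed models with unstructured covariance were simulated, 300 to 350 runs per case, with N = 80 complete, N = 80 with 30% dropout unrelated to the data, and N = 56 complete. Average model standard errors compared as follows.

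- Equal slopes: the interaction model's was 0.2% to 0.6% larger.
- Mild decay (0.70/0.65/0.60): level, with the common slope 0 to 0.2% smaller.
- Strong or autoregressive decay: the interaction model's was 1% to 3% smaller.

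**4. Bias under baseline-related dropout.** Assumptions: no true effect, SD 2, about 31% to 33% dropout after day 60, follow-up correlations of 0.8 (adjacent) and 0.7 (days 60 to 180), and log-odds of dropout changing by 0.8 per baseline SD.

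- Dependence in one arm only: the common-slope model was off by about 0.05 points under mild decay and about 0.10 under strong decay.
- Dependence in opposite directions by arm: up to about 0.2 points.
- With baseline×time the estimate stayed within simulation noise of zero. With equal slopes neither model was biased.
- Cost: with equal slopes and opposite-direction dropout, the interaction term raised the standard error by up to about 2%.

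**5. Observed discontinuation.** 14/58 = 24% of those enrolled; 14/(33 + 14) = 14/47 = 30% of those with a known outcome.

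**The case against.** The strongest reply is that nothing here is an error. A mixed model with baseline as a plain covariate is valid and widely used, and randomisation keeps the contrast essentially unbiased with complete data. That stands, and it is why the point is minor.

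The article is also a condensed account. It does not say that an interaction is excluded, and a fuller plan may contain one. A reader might infer that the sponsor has deliberately constrained the slope; the text does not support that. What can be said is that the model is listed term by term and this term is not in the list.

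A reader might also infer that precision is certainly being lost. The documents do not show this. They give "a correlation coefficient of 0.60" and nothing by visit; used at every visit with equal SDs, it implies no loss at all. Nor does a falling correlation by itself mean a falling slope: correlations of 0.70/0.65/0.60 with follow-up SDs of 1.00, 1.08 and 1.17 times the baseline SD give slopes of 0.70 × 1.00, 0.65 × 1.08 and 0.60 × 1.17, all about 0.70, and the loss vanishes.

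Finally, the term is not free at this sample size, as the simulations show. The bias figures need both decaying slopes and dropout that depends on baseline differently by arm. The article reports neither, and it does not split the 14 discontinuations by arm.

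**Conclusion.** The point holds as a minor improvement. As listed, the primary model uses one baseline slope for three visits while its contrast is read at the last. The consequence ranges from nothing (equal slopes) to about 3.6% of the day-180 standard error, or 2.8 power points at 40 per arm, under the steepest decay assumed. The further risk is a bias of roughly 0.05 to 0.2 points against a planned 1.0, conditional on arm-specific, baseline-related dropout. That risk deserves some weight because follow-up ends at discontinuation, discontinuation is already 24% of those enrolled, and the missing-at-random analysis runs through this model. All these sizes rest on assumed visit-specific correlations, equal SDs and assumed dropout patterns. They do not show that the planned analysis is invalid or that its result will be biased.

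**What to change.** Add a baseline×time interaction to the primary mixed model and estimate the treatment difference at day 180 from it. If the full analysis plan already includes the term, saying so is enough.

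The cost is two extra parameters. If the slopes turn out equal, the standard error rises by about 0.2% to 0.6%, or up to about 2% if dropout depends on baseline in opposite directions by arm. No new data are needed. The trial is still running, no interim analysis is planned and the data analyst is blinded to allocation, so the change can be recorded before unblinding.
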